# Personal innovative approach in radiation therapy of lung cancer- functional lung avoidance SPECT-guided (ASPECT) radiation therapy: a study protocol for phase II randomised double-blind clinical trial

**DOI:** 10.1186/s12885-021-08663-1

**Published:** 2021-08-21

**Keywords:** Lung cancer, Radiation therapy, Radiation-induced lung toxicity, Functional imaging, Perfusion SPECT/CT

## Abstract

**Background:**

Radiation therapy (RT) plays a key role in curative-intent treatment for locally advanced lung cancer. Radiation induced pulmonary toxicity can be significant for some patients and becomes a limiting factor for radiation dose, suitability for treatment, as well as post treatment quality of life and suitability for the newly introduced adjuvant immunotherapy. Modern RT techniques aim to minimise the radiation dose to the lungs, without accounting for regional distribution of lung function. Many lung cancer patients have significant regional differences in pulmonary function due to smoking and chronic lung co-morbidity. Even though reduction of dose to functional lung has shown to be feasible, the method of preferential functional lung avoidance has not been investigated in a randomised clinical trial.

**Methods:**

In this study, single photon emission computed tomography (SPECT/CT) imaging technique is used for functional lung definition, in conjunction with advanced radiation dose delivery method in randomised, double-blind trial. The study aims to assess the impact of functional lung avoidance technique on pulmonary toxicity and quality of life in patients receiving chemo-RT for lung cancer. Eligibility criteria are biopsy verified lung cancer, scheduled to receive (chemo)-RT with curative intent. Every patient will undergo a pre-treatment perfusion SPECT/CT to identify functional lung. At radiation dose planning, two plans will be produced for all patients on trial. Standard reference plan, without the use of SPECT imaging data, and functional avoidance plan, will be optimised to reduce the dose to functional lung within the predefined constraints. Both plans will be clinically approved. Patients will then be randomised in a 2:1 ratio to be treated according to either the functional avoidance or the standard plan. This study aims to accrue a total of 200 patients within 3 years. The primary endpoint is symptomatic radiation-induced lung toxicity, measured serially 1–12 months after RT. Secondary endpoints include: a quality of life and patient reported lung symptoms assessment, overall survival, progression-free survival, and loco-regional disease control.

**Discussion:**

ASPECT trial will investigate functional avoidance method of radiation delivery in clinical practice, and will establish toxicity outcomes for patients with lung cancer undergoing curative chemo-RT.

**Trial registration:**

Clinicaltrials.gov Identifier: NCT04676828. Registered 1 December 2020.

**Supplementary Information:**

The online version contains supplementary material available at 10.1186/s12885-021-08663-1.

## Background

Lung cancer is the most commonly diagnosed cancer worldwide and one of the leading causes of cancer death with very poor prognosis [1]. Concurrent chemo-radiation therapy (RT) plays a significant role in the treatment, as up to 77% of all lung cancer patients may require RT at some point during the treatment [1]. Despite that, many patients do not receive this treatment due to concerns about radiation-induced lung toxicity (RILT). Up to 50% of patients may develop clinical signs of RILT weeks and months after RT, such as dyspnea, cough, chest pain and fever [2]. These symptoms may become chronic and reduce the patient’s reserve to deal with future cardiopulmonary stresses and receive anti-cancer therapy in the future [2, 3]. The condition may become life-threatening, whereas the development of RILT in some cases has shown to negatively affect patient’s survival [4]. Furthermore, the addition of 1 year of maintenance anti-PD-L1 therapy after definitive chemo-RT has become a new standard-of-care for patients with stage III non-small-cell lung cancer. In phase III PACIFIC clinical trial maintenance durvalumab have shown clinical benefits, but also potential for increased toxicity [5]. Given the morbidity associated with RILT and its increasing relevance in lung cancer, our ability to identify patients at risk for developing treatment related toxicity is crucial. Therefore, RT is a trade-off between eradicating the tumour and minimizing damage to the lung. The ability to avoid well-functioning lung tissue around the tumour points to a significant gap in our current treatment paradigm. An important assumption in RT is that functional activity is distributed homogeneously throughout the lungs. However, a significant proportion of lung cancer patients have defects in regional lung function caused by tumour, chronic lung disease and smoking [6]. For these patients undergoing potentially toxic therapy, pre-treatment assessment of lung function is very important. Single photon emission computed tomography (SPECT) is a well-established functional modality for diagnosis and monitoring of lung disease [7]. SPECT uses radioactive labelled tracer for imaging pulmonary circulation, where perfused areas equate with normal functional lung. Fused hybrid SPECT/CT images lung anatomy and function combined.

Over the last decade, several studies demonstrated that SPECT may be useful to guide radiotherapy to reduce RILT [8]. We have previously established the role of SPECT/CT in imaging of functional heterogeneity, prediction the risk of RILT, and showed dose-response relation [4, 6, 9]. The rationale of the functional lung avoidance approach is to guide the radiation away from functional lung regions. Thus, numerous studies demonstrated that incorporating functional imaging into treatment planning is feasible [8–12]. However, it remains to be proven clinically that functional image guided RT improves the toxicity outcomes of lung cancer patients. There is, therefore, a need for prospective interventional trials with clinical endpoints of radiation-induced toxicity to establish the role of functional lung avoidance RT in clinical practice. The ASPECT trial will implement functional imaging into radiotherapy of lung cancer to provide evidence for the effect of functional lung avoidance RT on clinical toxicity outcomes, quality of life, disease control and survival parameters.

## Methods/design

### General objective

To determine if SPECT-Perfusion Functional Avoidance improves toxicity outcomes for patients with lung cancer undergoing curative chemo-RT.

Endpoints.

The primary endpoint is symptomatic RILT, defined as number of patients developing pulmonary toxicity ≥ grade 2 in both treatment arms
Measured using the National Cancer Institute Common Toxicity Criteria (NCI-CTC) version 5 for radiation pneumonitis, dyspnea, cough, or any other radiation-induced respiratory, thoracic and mediastinal disorder. Measured serially from 1 to 12 months after RT

Secondary endpoints are:
Change in quality of life and patient reported lung symptoms according to the EORTC quality of life questionnaires QLQ-C30 and QLQ-LC-13. Measured serially from 1 to 12 months after RT.Dose-volume histogram parameters for lung and functional lungProgression-free survival, defined as time from randomisation to disease progression at any site or deathOverall survival, defined as time from randomisation to death of any cause or last date known aliveLoco-regional control rate at 12 months, defined as freedom from local disease progression 12 months after randomisation.

### Characteristic of the participants

Histologically verified lung cancer (small-cell and non-small-cell lung cancer)Referred for RT with curative intentRadiation dose of 50–66 Gy given in 2-Gy fractions, other dose levels and fractionation schedules accepted, as per site standardConcurrent chemotherapy is acceptedConcurrent immunotherapy is not allowedPrevious RT to the thorax region is not allowedPatients with oligometastatic disease are allowed, where metastasis have been ablated with surgery or RT, receiving (chemo)-RT to the thoracic disease with curative intentAbsence of other uncontrolled malignanciesAbsence of any psychological, familial, sociological, or geographical condition potentially hampering compliance with the study protocolAdults over 18, that have given oral and written informed consent before patient registration

### Study design

This study is a multicentre non-comparative double-blinded randomised phase II trial (Fig. 1). Participation implies baseline and follow-up procedures as indicated in Table 1. SPECT/CT will be performed on all patients included in the trial prior to randomisation. In the treatment planning phase, a standard and a functional avoidance plans will be produced for each patient. The patients will be randomised to one of the following arms: Arm 1- Functional avoidance radiation therapy and Arm 2- Standard radiation therapy.

**Fig. 1 Fig1:**
[figure not shown]
ASPECT study design

**Table 1 Tab1:** Summary of baseline and follow-up investigations

Required Investigations	Baseline	1 month	3 months	6 months	9 months	12 months
Subjective						
QLQ-C30 + LC13	X	X	X	X	X	X
Objective						
Physical examination	X	X	X	X	X	X
Toxicity scoring (CTCAE v5)	X	X	X	X	X	X
Management						
Medication	X	X	X	X	X	X
Analytic						
Blood samples	X		X	X		X
Lung function tests PFT, DLCO	X			X		X
Progress CT evaluation	X		X	X	X	X
SPECT/CT	X					
Adverse Events	X	X	X	X	X	X

Patient recruitment and data collection will take place at academic and regional Hospitals with expected 3–5 study sites in Denmark and Australia.

### Study procedures

#### SPECT/CT scan

In the lung, perfusion SPECT is able to image functioning pulmonary vasculature. SPECT perfusion imaging is acquired using a Siemens dual head SPECT-CT gamma camera (Symbia or Intevo), following intravenous injection of approximately 200 MBq of 99mTc - macro-aggregated albumin with the patient supine, typically in an arms-up position. A “step and shoot” methodology is used for data acquisition, with high-resolution collimation, 32 steps per head at 20 s per step. Low dose CT is concurrently acquired, without breath-hold, using parameters of 110 kV and 50mAs. Processing is via an ordered subset technique, using 6 subsets and 4 iterations with attenuation correction using CT data, as well as scatter and resolution recovery techniques, for more quantitatively robust MAA SPECT data. Patient positioning and fixation is done according to the standard procedures of the Nuclear Medicine Department. Total functional lung (FL) (all voxels with SPECT signal in the lungs excluding gross tumour volume (GTV)) is contoured. In addition, contours of functional lung are created from the SPECT signal using a threshold of 20–80% of maximum perfusion count (FLx, x = 20, 40, 60, 80%) for each patient individually, as described previously [9, 12]. These contours are transferred from the SPECT/CT to the planning CT using rigid registration and cropped to the delineated total lung volume.

#### Radiation therapy

Recommendations for radiation treatment of lung cancer developed by the Danish Oncologic Lung Cancer Group (DOLG) will be applied and used for planning scan, fixation technique, planning algorithm, target definition and coverage, image guidance, fractionation, organs at risk delineation and dose constraints [1]. Local treatment centres and research protocols guidelines may be applied. Radiotherapy regimen involves Positron emission tomography (PET/CT)-based dose planning. Radiation doses are delivered to the target with a minimization of associated irradiation of surrounding normal tissue. All patients, regardless participation in the trial will be treated with a prescribed dose to the target.

#### Patient data acquisition and patient positioning

Patients undergo free breathing PET/4DCT scan in the supine position (helical CT scanner with minimum 3 mm slice spacing). The patients are reproducibly fixated and immobilized. The scan is performed after injection of intravenous contrast, and the scan range covers the complete thoracic region.

#### Target delineation

All CT scans are transferred to the treatment planning system and GTV of the primary tumour and involved nodes as defined by FDG uptake on PET scan or positive histology from biopsy. GTV is expanded to a clinical target volume (CTV) by adding isotropic margins for primary tumour and for nodes. CTV can be modified in areas of overlap with large vessels, bones, trachea, chest wall and lung tissue without compromising the GTV – though never if the GTV extends into the adjacent tissue. By adding margins to the CTV to generate a planning target volume (PTV), it is ensured that the CTV is covered by the planned dose. These margins take into account the uncertainties associated with planning and treatment delivery. Margins must be supported by the image-guidance recommendations from DOLG guidelines. Respiratory motion can be included either in the delineation of the GTV or as a patient specific part of the PTV margin.

#### Organs at risk (OAR) delineation and constraints

The organs at risk are: lung parenchyma, esophagus, spinal cord, heart and body. Dose constraints to organs at risk are respected to minimize the risk of complications. The constraints on the spinal cord, heart and the volume of the lung receiving at least 20 Gy are following (unless otherwise specified for patients included in other protocols)
Both lungs should be contoured in their entirety. The mean lung dose (MLD), the mean dose delivered to both lungs minus all GTV’s) will be calculated from dose-volume histogram (DVH) and should not exceed 20 Gy. The V_lung_20 (the volume of lung outside the tumour receiving a dose of more than 20Gy) should not exceed 35%, aim for V5 < 60%;The esophagus volume (outer muscular contour) must be contoured from the level of just below the larynx to the gastro-esophageal juncture. The PTV should not be subtracted from the total volume of the esophagus. Aim for dose to 1 cm^3^ under 100% of prescribed dose;For spinal cord dose evaluation, it is mandatory to contour the spinal cord. The calculated near maximum dose to the spinal cord should not exceed 45 Gy or max 50 Gy for delineated spinal canal;The heart dose should be kept as low as possible, following the constraints of V40 < 30% and V25 < 50%;Body: global hotspot< 112%.

#### Dose specification

After contouring the target and normal structures, photon treatment plans are created, using a modern advanced planning technique. Inhomogeneity corrections and advanced dose calculation algorithms (Monte Carlo, Acuros, AAA, Collapsed Cone or equivalent) have to be used. The plans are optimized to keep the dose to normal tissue as low as possible and to respect the specified OAR constraints. The margin from CTV to PTV must be sufficient to ensure that 100% of the CTV volume is covered with at least 95% of the prescribed dose. These dose constraints and recommendations for dose to OARs apply regardless of randomisation to the SPECT or standard plan arm.

#### Patient setup and in-room imaging

For every treatment session, the internal target position is verified using a kV cone beam CT scan acquired in the treatment position. The patient position is corrected before treatment to ensure that the primary tumour and lymph nodes are as close to the planning situation as possible. Adaptive re-planning criteria are left up to the implemented guidelines for systematic adaptive treatment strategies.

#### SPECT/CT planning and optimisation technique

New contours of functional lung identified as 20–80% subvolumes of the maximum perfusion count (FL20–80) are used in a second optimization to avoid high radiation doses to the best functioning lung tissue. The principal objective for functional avoidance is to reduce dose to the highly perfused lung subvolumes without compromising PTV coverage and to minimise a dose variation within the PTV. Dose constraints for other OAR should be respected and kept within the predefined constraints, described above.

For each patient, two treatment plans will be generated:
A standard reference plan, based on CT alone, blinded to functional structuresA functional avoidance plan, SPECT-plan, imposing higher priority on functional levels.

Functional avoidance RT planning objectives are:
To obtain lower (as low as possible) doses to FL volumes, while maintaining CTV/PTV coverage.Dose to organs at risk must be kept within the specified above dose constraints.

The standard plan is used as a basis for optimization of the functional avoidance plan.

The following mean constraints are added to keep anatomical lung and heart doses similar between the two plans. Relative tolerated change (△) in dose-volume parameters for OARs (+/−):
total lung △mean Dose ≤1.5 Gyheart △mean Dose ≤1.5 Gy

Provided it still meets all normal tissue constraints described above.

Results of the feasibility study of standard and functional avoidance plans comparison between two participating centres are presented in Additional file 1.

#### Randomisation and blinding procedures

After both plans have been approved and accepted for treatment, randomisation will take place electronically. Participants will be randomly assigned to either experimental or control group with a 2:1 allocation as per a computer-generated randomisation schedule stratified by disease stage, concurrent chemotherapy, and treating institution, using permuted blocks of random sizes. The block sizes will not be disclosed, to ensure concealment. Data Manager of Clinical Research Unit will generate allocation sequence and assign participants to intervention. Allocation concealment will be ensured, as the service will not release the randomisation code until the patient has been recruited into the trial, which takes place after all baseline measurements have been completed, and two treatment plans have been approved. Randomisation will be requested from Clinical Research Unit, which will send the result to the dose planner/physicist and research coordinators who are not involved in direct patient care or study assessments. The correspondent radiation treatment plan will be sent through to the treatment Unit, while another one rejected in the treatment planning system. Information on the allocated Arm will be concealed from the treatment plan ID, and therefore concealed from radiotherapists/ radiation nurses in direct contact with the patient.

All participants and personnel involved in their medical care will be blinded to the allocated treatment arm. Research personnel, and planners/ medical physicists are unblinded. Unblinding of the treating radiation oncologist is permitted in case of serious adverse event, where treatment plan review is necessary. Unblinding of the treating radiation oncologist is also permitted in case of treatment adaptation.

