#### During treatment

The patient is seen by a physician on the day of the first, middle and last fraction, where toxicity is evaluated by CTC-AE v. 5, medication list updated, and quality of life assessed.

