#### After the end of treatment (follow-up)

Follow-up visits are scheduled for 1, 3, 6, 9 and 12 months after RT. Investigations during follow-up serve the purpose of monitoring radiation-induced toxicity and quality of life. In case of lung toxicity occurrence on the scheduled follow-up visits, as well as acutely, diagnostic and treatment procedures will be done as indicated by the standard diagnostic procedures. In case of disease progression, the patient will be treated according to regular department policy.

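### The treating oncologist may be unblinded at a serious adverse event or at adaptation, and nothing in the article keeps an unblinded oncologist from later judging RILT

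*Protocol article*

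**What the plan says.** All references are to the protocol article.

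- **Randomisation and blinding procedures** opens with a general rule: "All participants and personnel involved in their medical care will be blinded to the allocated treatment arm". Two exceptions follow. One is conditional: "Unblinding of the treating radiation oncologist is permitted in case of serious adverse event, where treatment plan review is necessary". The other has no further condition: "Unblinding of the treating radiation oncologist is also permitted in case of treatment adaptation".
- The same section lists staff who know the allocation: "Research personnel, and planners/ medical physicists are unblinded". The only stated separation from endpoint scoring concerns those who receive the randomisation result, the dose planner or physicist and "research coordinators who are not involved in direct patient care or study assessments". It is not extended to an oncologist unblinded later.
- **General objective (Endpoints)** defines the primary endpoint as pulmonary toxicity of grade 2 or higher under version 5 of the NCI criteria, measured serially from 1 to 12 months after RT. It covers pneumonitis, dyspnea, cough and any other respiratory, thoracic or mediastinal disorder caused by radiation.
- **During treatment** says "The patient is seen by a physician on the day of the first, middle and last fraction", "where toxicity is evaluated by CTC-AE v. 5". **After the end of treatment (follow-up)**, which covers the endpoint visits, names no scorer. For lung toxicity it says that "diagnostic and treatment procedures will be done as indicated by the standard diagnostic procedures".
- **Adaptation and re-planning** foresees repeat simulation, for example after tumour reduction or atelectasis, with a procedure that differs by arm. **Patient setup and in-room imaging** leaves the re-planning criteria to implemented guidelines.

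**The concern.** Two judgements decide whether a patient counts as a primary event: whether the grade reaches 2, and whether radiation caused the disorder. The blind is meant to protect both, and the two exceptions open it in different ways.

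- **Event route.** A serious lung event can be a primary event and also, if the plan must be reviewed, the occasion for unblinding. Nothing stated requires grade and attribution to be recorded first, so attribution to radiation rather than to infection, progression or a drug could be settled with the arm known.
- **Adaptation route.** Adaptation takes place during RT, before every endpoint visit. If the unblinded oncologist then sees the patient in follow-up, every later judgement can be made with the arm known, including the borderline call between grade 1 and grade 2 cough or dyspnea.

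The conclusion rests on the SPECT arm against a fixed 75%. A shift of a few patients in that arm goes straight into the result, and the concurrent control does not correct it. The same classifications feed the 50-patient futility analysis.

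**Working it through.** **Step 1: set the provisions side by side.**

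| Question | Event route | Adaptation route |
|---|---|---|
| Condition for unblinding | Serious adverse event, and plan review necessary | Adaptation; nothing further |
| Timing against the 1–12 month window | Can coincide with the endpoint event | During RT, before all endpoint visits |
| Judgement mainly exposed | Attribution, since a serious lung event usually lies well above grade 2 | Grade and attribution at each later visit |
| Rule that grade is recorded first | None stated | Not possible; no endpoint grade exists yet |
| Rule that later scoring passes to a blinded person | None stated | None stated |

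**Step 2: reproduce the plan's sample size.** Inputs from *Sample size*: freedom from RILT of 75% (uninteresting) and 84% (interesting), 95% confidence, at least 80% power, 130 SPECT patients. With X ~ Binomial(130, p), the smallest cut-off r with P(X ≥ r | 0.75) ≤ 0.05 is r = 106:

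- P(X ≥ 106 | 0.75) = 0.049
- P(X ≥ 106 | 0.84) = 0.814

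The smallest n meeting both conditions is 130, so the stated figure reproduces as a one-sided 5% exact design. With a 2:1 control arm, 130 + 65 = 195, as stated. The cut-off of 106 is derived here; the article does not print it.

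**Step 3: effect of events lost.** If k SPECT-arm events are classed as non-events, success needs only 106 − k patients truly free of RILT. The false-positive risk is P(X ≥ 106 − k | 0.75):

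| k | True number needed | False-positive risk |
|---|---|---|
| 0 | 106 | 4.9% |
| 1 | 105 | 7.5% |
| 2 | 104 | 11.0% |
| 3 | 103 | 15.5% |

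**Step 4: what it takes to reach such counts.** The documents give neither the share of events judged unblinded (u) nor the share of those reclassified (s); both are assumed. Observed freedom becomes 0.75 + 0.25 × u × s, and expected events lost are 130 × 0.25 × u × s = 32.5 × u × s.

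| u | s | Observed freedom | Events lost | False-positive risk |
|---|---|---|---|---|
| 10% | 1/10 | 0.7525 | 0.3 | 5.6% |
| 30% | 1/10 | 0.7575 | 1.0 | 7.2% |
| 10% | 1/3 | 0.758 | 1.1 | 7.5% |
| 30% | 1/3 | 0.775 | 3.3 | 15.9% |

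**Step 5: the opposite direction.** If knowing the arm inflates the event rate at a true 84% by 5% or 10%, freedom becomes 1 − 0.16 × 1.05 = 0.832 or 1 − 0.16 × 1.10 = 0.824. Power falls from 81.4% to 73.9% or 65.3%.

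**The case against.** Several points on the other side have force.

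- **A serious event is seldom borderline.** A lung event that prompts plan review will usually be clearly above grade 2, and that route is limited to cases needing plan review. This stands. It confines the event route mainly to attribution, and a reader who infers that the grade of the severest RILT is at risk goes further than a binary endpoint at grade 2 supports.
- **The article does not say that the treating oncologist scores the endpoint.** The sentence on a physician evaluating toxicity concerns visits during RT, and the follow-up section names nobody. This also stands: the documents support only that an unblinded oncologist can score, not that one will.
- **The full protocol may name a follow-up assessor and keep an unblinding log.** It may. But the article itself sets out who may be unblinded and when, and its one separation from assessments does not reach that person. The point is about a rule the article states, not about detail it condenses.
- **Adaptations are partly tracked.** The site investigator must be notified in connection with re-planning without functional volumes, and randomised patients not treated on the allocated plan are described with reasons. This is correct, but neither step records the unblinding or protects later scoring.
- **The size is assumed.** It is. With one tenth of unblinded events reclassified, the risk is about 6% to 7%; only with one third does it reach about 16%. The bias could also run the other way.

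**Conclusion.** The point holds in a limited form. The article permits the treating oncologist to be unblinded by two routes and does not keep that person from later judging RILT. The event route exposes mainly the attribution to radiation; the adaptation route exposes any grade or attribution at the 1 to 12 month visits and is the wider of the two.

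The false-positive figures of 7.5%, 11.0% and 15.5% for 1, 2 or 3 reclassified events show how little movement the design tolerates. They assume 130 evaluable SPECT patients, the derived cut-off of 106, and reclassification in one direction only. They do not estimate what will happen. A reader might infer that the double blind has failed or that the error rate will be inflated; with no frequency of unblinding, adaptation or reclassification in the documents, neither inference is supported. The sample size is unaffected. The change is worth making because it is cheap and the gap follows from a stated rule.

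**What to change.** 1. **Event-triggered unblinding.** Record and lock CTCAE grade, onset date and attribution in the database before the code is released. Where urgent safety needs prevent this, release the code and note that the lock was not possible.
2. **Log.** Record date, reason and person unblinded for every unblinding, including those at adaptation.
3. **Later scoring.** For every patient whose oncologist was unblinded, have follow-up CTCAE scored, where available, by a site clinician who already sees trial patients and has not been unblinded. This is the step that addresses adaptation; a lock cannot, because no endpoint grade exists at that time.
4. **Sensitivity analysis of the primary endpoint.** Use the locked grade where one exists. As a conservative bound, count any pulmonary grade 2 or higher scored after unblinding as an event regardless of attribution. Label this bound as departing from the primary endpoint definition, since it will include some infection or progression. It does not recover an event scored down to grade 1, which is why step 3 is needed.

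Safety access to the allocation and the number of patients stay as they are. The cost is brief data entry, a log, some rearrangement of who scores at follow-up, and one additional analysis.
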